**Fig. 4 Fig4:**
[figure not shown]
Flow chart. Assessment of unintended medication discrepancies. BPMH = best possible medication history, ICU = intensive care unit, MTE = medication transfer error, PDMS = patient data monitoring system

The secondary outcome measure of this study is the proportion of patients with a potential adverse drug event (pADE) score due to an MTE, both at the moment of admission and at the moment of discharge. In addition, the pADEs scores and the associated costs are secondary outcome measures. A pADE score is defined as a potential and severity score for discomfort, harm and/or clinical deterioration caused by an unintentional discrepancy [19].

Determination of the potential and severity that a patient will experience harm due to an MTE will be based on the methodology described by Nesbit et al [19]. The same method was recently used by Gallagher et al [20]. This method uses the following categories for probability and severity of harm: 0 (zero; no harm expected by the MTE), 0.01 (very low: some harm is expected, but not clinically relevant), 0.1 (low: some harm is expected but poorly clinically relevant), 0.4 (medium; harm is expected, clinically relevant) or 0.6 (high; harm is expected, life threatening). In order to assign the probability and severity category for each MTE, we will present all MTEs at ICU admission or discharge to two assessors; one hospital pharmacist/clinical pharmacologist and one internist/clinical pharmacologist in training, who will, independently from each other, make a judgment based on clinical data of the patient. In case of differences between the judgments, the assessors will come together to reach consensus. If consensus cannot be reached, the case will be presented to a internist/clinical pharmacologist, who will make the final decision.

Next, our preliminary cost-effectiveness analysis will estimate the incremental costs per prevented MTE of the TIM compared to usual care, from the hospital’s perspective. Costs will comprise both the costs incurred by the reconciliation process and cost avoidance due to preventing MTEs and their pADEs.

The cost avoidance of the TIM program will be determined through summation of the individual pADE judgment scores of the MTEs and multiplying it by the cost of an ADE in the pre-intervention period compared to the post-intervention period.

For measuring the cost of an ADE, we will estimate the medical consumption associated with the consequences of harm, such as number of ICU days and medical specialist- and nursing staff time, by means of expert opinion and by using previous literature [7, 9, 19–21]. These will be valued using the reference prices of the ‘Dutch Manual for Costing’ [22]. In case reference prices are not available, medical consumption will be valued with the tariffs provided by the Dutch Healthcare Authority [23]. Costs of potential adverse drug events will be estimated using previous literature [6–8, 10].

Costs incurred by the reconciliation process are restricted to labour. The number of minutes spent per patient by the pharmacist will be measured during the intervention. These minutes will be valued based on standardised costs per minute, which equal the normative income of the pharmacist (collective labour agreement) divided by the number of workable minutes per year [24].

All costs will be based on Euro cost data. If necessary, costs will be adjusted to the year of data collection using the general price index from the Dutch Central Bureau of Statistics [23].

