### Design

A prospective 8-month observational study with a before and after design will be carried out at Haga Teaching Hospital in The Hague (650 bed general teaching hospital with 18 ICU beds; 1500 ICU admissions a year) and Erasmus Medical Center in Rotterdam (University Hospital, 1320 beds and 32 ICU beds; 1800 ICU admissions a year). Both hospitals are located in the Netherlands.

The study consists of three periods: first, a pre-intervention period of 14 weeks during which patients will be included who receive usual care; second, a period of 4 weeks during which the TIM intervention program will be implemented, and finally, a post intervention period of 14 weeks during which patients will be included in the TIM program (Fig. 1).

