#### TIM program at ICU discharge

When a patient is discharged from the ICU, the pharmacist makes a discharge medication summary. This medication summary contains an overview of medications on the patient’s BPMH combined with all the medication the patient uses in the ICU at the moment of discharge. For each drug, the ICU doctor is given a series of options of recommendations (i.e.: restart, stop, continue), making it easier for the ICU doctor to provide clear prescription suggestions to the doctor of the general ward. The ICU pharmacist reconciles this medication list with the ICU doctor. During this reconciliation, special attention is paid to temporarily withheld medication that should be restarted and to temporary ICU medication that should be stopped. After this reconciliation, the pharmacist amends the medication list to establish the Best Possible ICU Medication Discharge List (BPMDL-ICU) (example in Fig. 2). Once the doctor has approved the BPMDL-ICU, it is combined with the discharge letter of the ICU and sent to the doctor of the regular ward at the moment of patient transfer.

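### The harm-scoring procedure states no masking of the assessors to study phase, so a phase-related lean could enter the pADE scores and the cost avoidance

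*Protocol article*

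**What the plan says.** The procedure is in the protocol article under Outcome measures. The investigators write that "we will present all MTEs at ICU admission or discharge to two assessors", a hospital pharmacist/clinical pharmacologist and an internist/clinical pharmacologist in training. The two are to "independently from each other, make a judgment based on clinical data of the patient". They assign each MTE a value of 0, 0.01, 0.1, 0.4 or 0.6 for the probability and severity of harm. "In case of differences between the judgments, the assessors will come together to reach consensus"; if they cannot agree, an internist/clinical pharmacologist decides.

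On the use of the scores: "In addition, the pADEs scores and the associated costs are secondary outcome measures", alongside the proportion of patients with a pADE. Cost avoidance is obtained by "summation of the individual pADE judgment scores of the MTEs and multiplying it by the cost of an ADE", comparing the pre-intervention with the post-intervention period.

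The Design section makes the two periods consecutive, starting with "a pre-intervention period of 14 weeks during which patients will be included who receive usual care". No section says whether the assessors are masked to period. The limitations in the Discussion mention the panel only because it judges potential rather than actual events.

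**The concern.** Scoring the harm of an error is a matter of judgement. An assessor who knows whether the error arose under usual care or under TIM may score it a little harder or a little more leniently without intending to. If both assessors know the phase, they can lean the same way. Independent scoring, consensus and a tie-break will not detect a lean that they share.

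Three secondary outcomes depend on these scores: the proportion of patients with a pADE, the pADE scores and the costs. Because cost avoidance is the summed score times a cost per ADE, a shift in scores between phases becomes an apparent saving even when harm per error has not changed. The steps of the scale are large (0.01 to 0.1 is tenfold, 0.1 to 0.4 fourfold), so few scores need to move.

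**Working it through.** **Would the clinical data reveal phase?**

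- Design: the 14-week periods are separated by a 4-week implementation period, so any calendar date identifies the phase.
- TIM program at ICU admission: the pharmacist enters the BPMH in the PDMS or HIS. The BPMH itself is compiled in both phases, so only this entry is a marker.
- TIM program at ICU discharge: the BPMDL-ICU exists only under TIM, and "it is combined with the discharge letter of the ICU and sent to the doctor of the regular ward".
- Data collection: the sources screened include hospital patient records and PDMS records, where such markers would be found.

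A panel reading the record unedited would therefore probably know the phase. The article does not say in what form the panel receives the data.

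**How large could the effect be?**

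The article gives no distribution of scores and no figure to reproduce on this point. Everything below is illustration under assumptions: no true difference in harm per MTE, equal numbers of MTEs in both phases, and a fixed cost per ADE. Percentages are of the pre-phase summed score, and so of the pre-phase ADE cost.

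Let B be the mean score, L the mean loss if every score dropped one category (0 stays at 0), G the mean gain if every score rose one category (0.6 stays at 0.6), and f the share of scores that shift.

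| Assumed % at 0 / 0.01 / 0.1 / 0.4 / 0.6 | B | L | G |
|---|---|---|---|
| Even: 20/20/20/20/20 | 0.222 | 0.120 | 0.120 |
| Low: 20/30/30/15/5 | 0.123 | 0.085 | 0.149 |
| Middle: 10/20/40/25/5 | 0.172 | 0.123 | 0.189 |

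Case 1, post-phase scores lean down only: fall = fL/B. 
Case 2, post-phase scores lean down and pre-phase scores lean up: post/pre = (B − fL)/(B + fG).

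Example, low mix, f = 10%: the case 1 fall is 0.0085/0.123 = 6.9%. The case 2 ratio is 0.1145/0.1379 = 0.830.

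| f | Case 1 fall (even, low, middle) | Case 2 post/pre (even, low, middle) |
|---|---|---|
| 5% | 2.7%, 3.5%, 3.6% | 0.947, 0.910, 0.914 |
| 10% | 5.4%, 6.9%, 7.2% | 0.897, 0.830, 0.837 |
| 20% | 10.8%, 13.8%, 14.3% | 0.805, 0.694, 0.703 |

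The case 2 ratios mean spurious falls of about 5% to 9%, 10% to 17% and 20% to 31%.

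Case 3, an extreme start: every MTE truly scores 0.1, and a share f of pre-phase scores is raised to 0.4. The pre-phase mean is 0.1(1 − f) + 0.4f = 0.115, 0.130 and 0.160 for f = 5%, 10% and 20%. The spurious fall is 1 − 0.1/mean = 13%, 23% and 37.5%.

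**Proportion of patients with a pADE.** The article states no threshold at which a score counts as a pADE. If any non-zero score counts, only shifts between 0 and 0.01 matter, and a move from 0.1 to 0.4 changes nothing. An effect here is possible but does not follow from the figures above.

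**The case against.** The strongest reply is that the article is silent, not contrary. A reader might infer that the assessors are unmasked and see dates and the BPMDL-ICU. The documents do not support that: they refer only to the patient's clinical data. The items listed under Patient data include no calendar dates, intervention programme data form a separate category, and the BPMDL-ICU is not among the sources named for screening. When scoring takes place is not stated either. A full protocol, not shown here, could specify masking. All of this stands, and it limits the point to what the article states.

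It does not remove the point. The article describes the scoring procedure in some detail, and each safeguard that it names addresses disagreement only. The change proposed replaces the stated procedure with one less open to bias, using the same assessors.

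Three other inferences go too far.

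- **Primary result.** The panel scores errors already classified as MTEs, so the primary proportions do not depend on it.
- **Size.** The 13% to 38% of case 3 are not an estimate. They come from starting every error at 0.1 and moving scores only across the fourfold step, and other mixes give much less.
- **Contrast with the earlier step.** One might argue that the panel can be masked because the preceding judgement of intent is made at the bedside. The article bases that judgement at admission on PDMS documentation, standards of care and the ICU pharmacist's interpretation. In the pre-intervention phase, the lists are compiled for patients at least 24 h out of the ICU. The text does not support that contrast.

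It is also fair to add that the cost-effectiveness analysis is described as preliminary.

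**Conclusion.** The point holds in a limited form. The stated harm-scoring procedure contains no masking to phase, its safeguards do not protect against knowledge of phase, and unedited clinical data would probably reveal it. Any resulting lean would pass into the pADE severity scores and the cost avoidance, and possibly into the proportion of patients with a pADE. The incremental cost per prevented MTE is touched only through its cost-avoidance term.

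The size cannot be determined from the documents. With 5% to 20% of scores moved by one category, the spurious change runs from about 3% (even mix, post phase only) to nearly 40% (all errors starting at 0.1). The shares, mixes and directions are all assumptions. This is an inexpensive improvement to secondary outcomes; it does not call the primary comparison into question.

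**What to change.** State that harm scoring takes place after both phases are complete. Pool all pre- and post-phase MTEs and present them in random order as standard case summaries. Remove calendar dates, TIM documents and pharmacist reconciliation entries. Use the same masked summaries at the consensus meeting and for the third assessor. Hospital identity need not be removed to mask phase, because both hospitals contribute to both phases. If masking is already specified elsewhere, one sentence saying so is enough; if it is not adopted, name it among the limitations.

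No extra patients or assessors are needed. The cost is the work of extracting and preparing the summaries, which may need clinical details beyond the listed CRF items (no laboratory values are listed, for instance), and some delay. The clinical content will occasionally reveal the phase. Masking the panel also leaves untouched any bias in the earlier classification of discrepancies as MTEs, which at admission rests partly on the ICU pharmacist's interpretation.

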#### TIM program, the intervention

The TIM program consists of medication reconciliation at ICU admission and at ICU discharge. In both intervention hospitals, the program will be carried out by two pharmacists. The pharmacists in Erasmus MC will be supported by pharmacy students, who, after a training period of several weeks, will be able to collect the medication lists and to interview the patients or their relatives about each patient’s pre-admission medication.

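### As written, avoided cost is a difference of period totals with no patient denominator, and labour cost names only pharmacist minutes although students share the reconciliation work

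*Protocol article*

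**What the plan says.** The economic rules are in the protocol article under Outcome measures.

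- **Target:** "our preliminary cost-effectiveness analysis will estimate the incremental costs per prevented MTE of the TIM compared to usual care". The viewpoint is that of the hospital.
- **Components:** "Costs will comprise both the costs incurred by the reconciliation process and cost avoidance due to preventing MTEs and their pADEs".
- **Avoided cost:** obtained by "summation of the individual pADE judgment scores of the MTEs and multiplying it by the cost of an ADE in the pre-intervention period". This is set against the post-intervention period. No patient or admission denominator is given.
- **Programme cost:** only staff time counts. On measurement, the article says: "The number of minutes spent per patient by the pharmacist will be measured during the intervention". Each minute is priced at a rate "which equal the normative income of the pharmacist (collective labour agreement) divided by the number of workable minutes per year".

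Other sections bear on these rules. Design and Sample size fix both phases at 14 weeks, and Study population takes in all eligible admissions in that time. Patients who die in the ICU count for the admission part only. Under TIM program, the intervention, the Erasmus MC pharmacists are "supported by pharmacy students, who, after a training period of several weeks, will be able to collect the medication lists". These students also interview patients or relatives. Under TIM program at ICU discharge, "The ICU pharmacist reconciles this medication list with the ICU doctor". Intervention program data lists interview time and a total reconciliation time among the data collected, without saying whose time it is.

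**The concern.** A sum of scores over a calendar window grows with the number of patients in the window. If the second window holds fewer patients, its sum is smaller even when TIM changes nothing, and the rule books the difference as avoided cost. If it holds more, part of a real effect is hidden. The labour term is on a different base, since it is measured per patient, so the two components cannot be combined until one is rescaled. The article does not say how.

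On the labour side, the rule names one staff group while the description of the intervention gives part of the work to another. In an analysis whose programme cost is labour and nothing else, the treatment of student minutes bears directly on the cost per prevented error.

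**Working it through.** The article states no figure for avoided cost or labour cost, so the figure to reproduce is the accrual estimate that sets the phase length.

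**1. Patients per phase (inputs from Sample size).** 133/(1 − 0.35) = 204.6, hence the stated 205. Weekly inclusions are admissions × 0.70 × 0.65/52:

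- Haga: 1500 × 0.455/52 = 13.125. Half of 205 takes 102.5/13.125 = 7.8 weeks (stated: 8).
- Erasmus MC: 1800 × 0.455/52 = 15.75, so 102.5/15.75 = 6.5 weeks (stated: 7).

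The stated weeks are reproduced. Over 14 weeks this gives 183.75 + 220.5 = 404.25, about 404 patients per phase. Erasmus MC supplies 220.5/404.25 = 54.5%.

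**2. Avoided cost from totals.** Let m be the mean summed pADE score per patient in the pre-phase, C the cost of an ADE, r the true relative reduction in the score and k = N_post/N_pre.

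- Totals: C·[N_pre·m − N_post·m·(1 − r)], which is 1 − k(1 − r) as a share of the pre-period cost.
- Per-patient difference scaled to N_post: k·r as the same share.

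With r = 0 the totals rule gives 1 − k = (N_pre − N_post)/N_pre, while the per-patient rule gives zero for every k. The planned 50% reduction refers to errors; I assume here that it carries over to the scores.

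| k | Totals, r = 0 | Totals, r = 0.5 | Per patient × N_post, r = 0.5 | Ratio |
|---|---|---|---|---|
| 0.8 | +20% | 60% | 40% | 1.50 |
| 0.9 | +10% | 55% | 45% | 1.22 |
| 1.0 | 0 | 50% | 50% | 1.00 |
| 1.1 | −10% | 45% | 55% | 0.82 |
| 1.2 | −20% | 40% | 60% | 0.67 |

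A shift of 10% is about 40 of 404 patients. The discharge sum also moves with survival: ICU mortality of 40% (assumed) instead of the planned 35% changes its patient number by 0.60/0.65 = 0.923, a fall of 7.7%.

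**3. How large the distortion must be to exceed the effect.** Against the N_post scale the distortion is |1 − k| and the effect is 0.5k, so it exceeds the effect only if k < 0.67 or k > 2. Against the N_pre scale the distortion is 0.5·|1 − k| and the effect is 0.5, so it does so only if k > 2.

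**4. Student minutes.** The article gives neither the students' share nor their cost. Assume that they do a fraction f of the reconciliation minutes at Erasmus MC, with equal minutes per patient at both sites. Their share of all minutes is x = 0.545·f: 13.6%, 27.3% and 40.9% for f = 0.25, 0.50 and 0.75. Let ρ be the student cost per minute relative to a pharmacist. The true pharmacist-plus-student cost is proportional to 1 − x + ρx.

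- Student minutes left out: share of cost missed = ρx/(1 − x + ρx). With ρ = 0.25 this is 4%, 9% and 15%. It is zero if students cost the hospital nothing (ρ = 0), and 14%, 27% and 41% if ρ = 1.
- Student minutes priced as pharmacist minutes: overstatement = (1 − ρ)x/(1 − x + ρx). With ρ = 0.25 this is 11%, 26% and 44%. It is zero if ρ = 1.

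**The case against.** The strongest reply is that the sentence on cost avoidance is loosely worded. It does not say that raw totals are subtracted, labour is recorded per patient, and a per-patient comparison may have been meant. The analysis is called preliminary, and an article condenses a fuller document. This stands as far as intent goes. But the article does state an operational rule, and an analyst who follows it obtains totals. The remedy is one sentence.

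Second, student time may already lie inside the total reconciliation time listed under Intervention program data. That is possible. The only stated rate is the pharmacist's, so those minutes would then be overpriced instead of omitted. Whether the hospital pays the students at all is not stated.

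A reader might go further and infer that the labour rule always flatters TIM because ICU-doctor time is ignored. The documents do not support this. In usual care, doctors already establish the medication history and write discharge letters, and ward doctors transcribe the orders. Under TIM the pharmacist enters the history, the discharge options are meant to make the ICU doctor's task easier, and at Erasmus MC the ward doctor has only to authorise a prepared list. Only the increment matters, and its sign is unknown.

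A reader might also infer that shifts in patient numbers could swamp the effect. At the planned 50% reduction, post-phase numbers would have to fall by a third or double. A smaller true effect lowers that threshold, but nothing in the article points to shifts of that size.

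**Conclusion.** The point holds in a limited form. Read as written, avoided cost carries an error of (N_pre − N_post)/N_pre of the pre-period cost when TIM has no effect: 10% for about 40 fewer patients, zero for equal numbers, and of either sign. The 404 patients per phase rest on the article's own accrual assumptions; the size of any imbalance is an assumption.

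The labour rule does not match the description of who does the work. Its error can go either way, depending on whether student minutes are dropped or priced as pharmacist minutes. The percentages in the working rest on assumed student shares and rates; the 14% to 41% figures are shares of minutes, and become shares of cost only if a student minute costs as much as a pharmacist minute.

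It would be too strong to call both cost terms simply wrong, or to predict that the corrected cost per prevented error will be less favourable. The matter is confined to a secondary, preliminary economic outcome and leaves the primary analysis of medication transfer errors untouched.

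**What to change.** 1. Define avoided cost and prevented errors as differences in per-patient means: at admission over all included patients, at discharge over patients discharged alive. Scale both to one common number of patients, with one common share discharged alive (w). Per included patient, net cost = mean labour cost − C·(Δscore_adm + w·Δscore_dis), and prevented errors = Δerrors_adm + w·Δerrors_dis. The common number cancels in the ratio.
2. Record who spent the reconciliation minutes (pharmacist or student), and value student minutes at what they cost the hospital, including zero if that is the case.
3. For ICU-doctor time, count only the increment over usual care, or state that it is excluded and vary it in both directions in a sensitivity analysis. Logging doctor minutes in the post-phase alone would charge TIM with gross time and introduce a new bias.

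The cost is a few sentences of analysis text and a staff-type field beside the existing time fields. Measuring incremental doctor time would also need some timing under usual care; where that is not feasible, the stated exclusion with a sensitivity analysis is enough.

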### Data collection

We will screen hospital patient records, PDMS records, CPOE/CDS medication lists, BPMH and BPML-GW24. Collected data from these sources will be categorized into three groups: patient data, medication data and intervention program data. Data will be collected in case report forms (CRFs). All data input in the CRF will be cross-checked by two pharmacists.

